## Enrollment

At the enrollment visit, the participant’s laboratory results will be reviewed with the study participant. Another rapid HIV test will be performed. All eligibility criteria will be reviewed and confirmed. If the participant is eligible, he or she will be enrolled and randomly assigned into one of 6 arms of this 3 condition cross-over study (see section 7.5). Each arm will be stratified by gender. The 4 doses/week group will occur on Monday, Tuesday, Thursday, and Friday, and the 2 doses/week will occur on Tuesdays and Wednesdays. Enrollments may be scheduled on any day of the week, but study drug initiation will occur at the beginning of the week (Monday for the 4 and 7 doses/week groups and Tuesday for the 2 doses/week group).

Blood, hair, and urine specimens will be collected at the enrollment visit. Participants will receive a detailed daily dosing schedule and visit calendar for all 3 periods of their study participation. The participants’ cell phone number, other phone numbers and a list of places where they might be located will be obtained along with a follow-up plan in the event that the participant is not at the designated meeting place.  A one-week supply of back-up medication will be provided in the event that participants are unable to be seen for directly observed doses. Study participants will be provided access to a 24 hour, 7 days/week emergency pager to discuss any potential study related adverse events with a study clinician.

| **Enrollment Visit** | |
| --- | --- |
| Component | Procedure/Analysis |
| Administrative | - Assign Participant ID or Screen failure ID - Review/update locator information - Provide lab results to participant - Confirm eligibility - Follow procedures for randomization assignment - Explain mDOT procedures - Confirm cell-phone number for doses observed by phone and reminder text messages - Provide dosing schedule and visit calendar to participant - Schedule next study visit with RA - Provide reimbursement for visit |
| Clinical | - Update medical history - Update list of concomitant medications - Perform full physical exam - Provide counseling   - HIV pre- and post-test counseling |
| Urine | - Collect urine sample   - Qualitative hCG   - Dipstick UA (and full UA with microscopy if greater than trace protein, glucose, heme, or leukocytes) |
| Blood | - Collect blood samples   - Complete blood count   - Serum chemistries   - Liver function tests   - Total serum lipase   - HIV-1 rapid test (confirmatory testing as needed)   - PBMC, plasma, and serum storage |
| Hair | - Complete standard hair collection questionnaire - Collect scalp hair sample - Self-collection of pubic hair sample (optional, opt-in procedure) |
| Study Product Supply | - Provide 1 week supply of back-up medication - Administer first dose (or schedule date of first dose) |

## Allocation Scheme

| **Sequence** | **N** | **Period A:**  **6 weeks** | **Break** | **Period B:**  **6 weeks** | **Break** | **Period C:**  **6 weeks** |
| --- | --- | --- | --- | --- | --- | --- |
| 1 | 4 (2M, 2F) | 7 doses/week |  | 4 doses/week |  | 2 doses/week |
| 2 | 4 (2M, 2F) | 7 doses/week |  | 2 doses/week |  | 4 doses/week |
| 3 | 4 (2M, 2F) | 4 doses/week |  | 7 doses/week |  | 2 doses/week |
| 4 | 4 (2M, 2F) | 4 doses/week |  | 2 doses/week |  | 7 doses/week |
| 5 | 4 (2M, 2F) | 2 doses/week |  | 7 doses/week |  | 4 doses/week |
| 6 | 4 (2M, 2F) | 2 doses/week |  | 4 doses/week |  | 7 doses/week |

## Randomization

The study statistician will randomize allocation sequences in two blocks of 6 within each gender stratum, (12 male and 12 female study participants). Each study participant will be randomly assigned to 1 of the 6 dosing sequences based on order of enrollment. Assignments will be concealed in sequentially numbered, opaque, sealed envelopes. Participants will be randomized to a sequence only after they have consented to participate, met eligibility criteria, and enrolled in the study.

## Follow-up Visits

Follow-up procedures at each visit are shown in Section 7.1. Adverse event assessments and symptom-directed physical exams will be performed by the study clinician every 3 weeks and additionally as needed during the study. The window period for scheduled study visits will be ± 5 days of the target visit date. Dosing will be continued at the assigned dosing frequency up until the endpoint visit occurs. No further doses for that dosing period will be given after the endpoint visit. HIV rapid testing and safety laboratory monitoring will also occur during these visits, and abnormal lab values will be followed clinically until stabilized. Adherence counseling will be performed at these visits. A hair sample will be collected on the last day of each treatment condition. Plasma samples for the intensive PK study will be collected after 4 weeks of dosing on the 7 doses/week condition.

## Directly Observed Visits and Phone Visits

Participants will receive modified directly observed dosing of oral TFV from a study staff according to the dosing schedules shown in section 7.2. Doses for all participants will be scheduled to occur at roughly the same time each day (e.g. 3pm). Ingestion of all Monday through Friday scheduled doses will be directly observed by study staff at an agreed-upon location on the UCSF campus, at the SFDPH research clinic, or at another predetermined location to maximize convenience for the participant. For weekends, holidays, and other foreseen-in-advance dates for self-dosing, study staff will provide pills to participants at the immediately preceding dose visit. Ingestion of unobserved doses will be confirmed via phone or text message mDOT. Participants will be asked to text or phone same-day confirmation of when they self-dose; if confirmation has not been received by a predetermined time, study staff will text and/or call asking for confirmation to help ensure that the doses are taken. Study staff will also send participants reminders as needed by email, text message, or telephone, for directly observed dose visits or to take back-up (emergency pack) medication if they miss a dosing visit. Dosing times will be recorded by the study staff for directly observed doses and telephone mDOT.  Study staff will confirm the dates and times of all self-administered doses at their next meeting with the subject.  Stipends will be provided at the completion of each dosing visit or clinical visit.

## Interim Contacts

Interim contacts and visits (those between regularly scheduled follow-up visits) may be performed at the participant request or as deemed necessary by the investigator or study staff at any time during the study. All interim contacts and visits will be documented in the participants’ study records.

## Criteria for Suspension of Study Product

Participants will be discontinued from receiving further study tablets for the following reasons:

- Confirmed HIV-1 infection
- Positive pregnancy test
- Positive hepatitis B surface antigen test or detectable Hepatitis B DNA
- Concurrent illness which, in the investigator’s opinion, may be exacerbated by continued product administration, requires treatment which is contraindicated by the protocol, jeopardizes further compliance or follow-up, or may confound the interpretation of adverse events
- Unacceptable toxicity, as defined in the toxicity management section of the protocol
- Participant request to discontinue for any reason
- Any clinical or social situation that, in the opinion of the investigator, jeopardizes compliance with the study product or confounds the interpretation of clinical adverse events

## Follow-up Procedures for Participants who Discontinue Study Product

Participants who discontinue study product will be encouraged to remain in the study if they are willing, for safety evaluations every 3 weeks according to the follow-up schedule in section 7.1. Since these participants will be off study drug, they will not complete directly observed or phone mDOT dosing visits. All study procedures described in the early study termination visit (in section 7.12) will be performed at the study drug discontinuation visit, including **hair** collection and PBMC**,** plasma, and serum collection. In addition, if a participant is advised to discontinue study drug by a clinician or the Principal Investigator during a dosing cycle due to an intercurrent illness, adverse event, or other circumstance, the participant may restart the unfinished dosing cycle at a later date if determined to be safe and appropriate by the Principal Investigator and allowable per protocol. Upon restarting the interrupted dosing cycle the participant would be required to complete the cycle in its entirety. This would include a start visit, midpoint visit, and an endpoint visit including all procedures and safety lab tests that are performed at each of these clinical visits. The process of repeating a dosing cycle will be at the discretion of the Principal Investigator. Participants who discontinue study drug and do not restart the dosing cycle will not participate in the intensive PK assessment after study drug discontinuation.

## Early Study Termination Visit

If a participant terminates study participation prior to the end of the study, he/she will be asked to have an Early Study Termination Visit and return any unused study product. At this visit, any evaluations showing abnormal results where there is a reasonable possibility of a causal relationship with the study drug should be repeated until the abnormality resolves or stabilizes. The following evaluations will be completed at the Early Study Termination Visit:

| **Early Study Termination Visit** | |
| --- | --- |
| Component | Procedure/Analysis |
| Administrative | - Provide lab results to participant - Provide reimbursement for visit |
| Clinical | - Review adverse events and intercurrent illnesses - Update list of concomitant medications - Perform symptom-directed PE - Provide counseling   - HIV pre- and post-test counseling |
| Urine | - Collect urine sample   - Qualitative hCG   - Dipstick UA (and full UA with microscopy if greater than trace protein, glucose, heme, or leukocytes) |
| Blood | - Collect blood samples   - Complete blood count   - Serum chemistries   - Liver function tests   - Total serum lipase   - HIV-1 rapid test (confirmatory testing as needed)   - Hepatitis B serological testing (if susceptible)   - **PBMC, plasma, and serum storage** |
| Hair | - Collect scalp hair sample (if on current regimen within the last 4 weeks) - Self-collection of pubic hair sample (optional, opt-in procedure) (if on current regimen within the last 4 weeks) |
|  |  |
| Study Product Supply | - Collect unused study medication from the participant |

In the event of early termination, participants may be replaced at the discretion of the PI and study statistician.

# DATA SOURCES

## Study Eligibility Assessment

Participants will undergo face-to-face interviews at the screening and enrollment study visits with trained staff. The screening interviews will obtain information on demographics, hair color, and study eligibility criteria.

## Clinical Assessment

A symptom directed physical exam will be performed at screening and a complete physical exam will be performed at enrollment by a trained clinician. Clinical symptoms will be systematically assessed every 3 weeks for the duration of the study. The severity of clinical symptoms will be scored using the established National Institutes of Allergy and Infectious Diseases (NIAID) Division of AIDS (DAIDS) toxicity scale. Additional data will be collected regarding concomitant medication use.

## Toxicity Monitoring

Blood and urine will be obtained at screening, enrollment, and then every 3 weeks while on study drug for toxicity monitoring. The severity of laboratory toxicity will be assessed and scored according to the DAIDS Toxicity scale (see section 9.6). Routine toxicity monitoring will include hematologic profile, chemistry profile (including sodium, potassium, chloride, total CO2 or bicarbonate, blood urea nitrogen, creatinine, random glucose, total bilirubin, alkaline phosphatase, phosphorus, AST, ALT, serum lipase), and urine dipstick.

## Monitoring for Pregnancy

Urine pregnancy testing will be performed for all female study participants at screening, enrollment, at every 3 week follow-up visit, and at the early study termination visit.

## HIV-1 Testing

HIV-1 serological testing will be performed using an FDA-approved whole-blood EIA rapid test at screening, enrollment, and every 3 weeks by trained study staff (except during breaks). Additional HIV serologic testing will be performed at interim visits on participant request. Non-reactive tests will be reported as non-reactive. Participants found to have reactive antibody tests will receive confirmatory testing with both a second FDA-approved EIA and WB or IFA.

## Hair Specimens

Hair specimens will be collected at enrollment and on the last day of each 6-week dosing period. A standard questionnaire will be completed at each hair collection visit to record information about hair treatments and type and number of hair samples collected. Hair specimens will be used to determine tenofovir hair concentrations under each dosing condition. Hair collection will be conducted by study staff trained on proper hair collection technique and will be stored at room temperature in aluminum foil in a secured, dark location until analyzed. Scalp hair will be collected on all study participants.

Participants will also be asked to provide a pubic hair specimen on an optional, opt-in basis using a self-collection technique. Pubic hair TFV level testing could be useful in certain parts of the world (e.g. sub-Saharan Africa) where men and women shave their heads or in individuals who dye their hair. Evaluating the correlation between scalp and pubic hair TFV concentrations will help determine whether pubic hair TFV testing could be a possible substitute for scalp hair in situations where scalp hair is unavailable. Those participants who agree to hair collection would be shown a sample of 200 pubic hairs and the proper technique for self-collection, including placement of a sticker on the distal end of the hair, cutting hair as close to the skin as possible, and placing hair in aluminum foil for storage.

All hair and blood samples (see sections 8.6 – 8.8) will be run in batch after all samples have been collected. The hair and pharmacology laboratory staff will remain blinded to the dosing condition until all testing is completed.

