**Exploratory Endpoints:**

- **Intracellular tenofovir concentrations.** The correlation between intracellular tenofovir-diphosphate concentrations and tenofovir hair concentrations on the last day of each dosing period will be determined.
- **HIV replication in vitro.** Dose and intracellular concentrations of tenofovir sufficient to render cells non-permissive for HIV-1 replication in vitro will be evaluated.
- **Pubic hair tenofovir concentrations:** TFV levels in scalp and pubic hair will be correlated under various dosing conditions.

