## Exploratory Objectives

- To determine the correlation between intracellular tenofovir diphosphate concentrations and tenofovir levels in hair under varying dosing patterns
- To determine dose and intracellular concentrations of tenofovir sufficient to render cells non-permissive for HIV-1 replication in vitro
- To determine the correlation between TFV scalp hair and pubic hair concentrations

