# STUDY DESIGN

This is a phase 1, open label cross-over study to evaluate the impact of varying dosing patterns on concentrations of TFV in hair among a cohort of 24 HIV-uninfected men and women. In addition, the study will determine how individual PK parameters at steady state impact TFV hair concentrations.

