## Study Primary Endpoint and Predictor Variables

Consistent with the primary study objectives, the following primary endpoint will be assessed:

- Tenofovir hair concentration: Tenofovir hair levels will be determined from a specimen containing 150-200 hairs collected at enrollment and on the last day of each period. For each participant, absolute hair levels and ratios of hair levels between conditions (7 vs. 4 doses/week, 4 vs. 2 doses/week, and 7 vs.2 dose/week) will be determined.

The following will be primary predictor variables:

- Dosing condition: The dosing condition will be examined as an ordinal variable: 2, 4, and 7 doses/week. We will also use actual percentage of total doses (by directly observed recorded doses and self-administered recorded doses) taken over the 6 week period as a continuous predictor of hair levels.
- PK parameters: The primary predictor variable of total exposure (PK contribution) will be oral clearance (CL/F). This variable is estimated by the equation “dose/AUC,” where AUC is the area under the plasma-concentration time curve for each intensive PK sampling procedure. Other parameters of drug exposure that will be evaluated as predictor variables include the concentration at the end of the dosing interval (trough or C_min_), peak plasma level (C_max_), and AUC alone. These PK variables will be calculated using non-compartmental methods.

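### Correlation alone is named to inform whether pubic hair could stand in for scalp hair; it cannot show a difference in level and, if pooled over dosing conditions, it partly reflects the assigned doses

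*Protocol*

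**What the plan says.** Three places in the protocol describe the scalp versus pubic comparison, and each names correlation and nothing else.

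- Section 4.2, Exploratory Objectives (repeated in the Protocol Summary): "To determine the correlation between TFV scalp hair and pubic hair concentrations".
- Section 2, Exploratory Endpoints: "TFV levels in scalp and pubic hair will be correlated under various dosing conditions".
- Section 8.6, Hair Specimens, which gives the purpose: "Evaluating the correlation between scalp and pubic hair TFV concentrations will help determine whether pubic hair TFV testing could be a possible substitute" where scalp hair cannot be obtained.

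On sampling, section 8.6 states that "Hair specimens will be collected at enrollment and on the last day of each 6-week dosing period", and that pubic hair is given "on an optional, opt-in basis using a self-collection technique". The study is carried out "among a cohort of 24 HIV-uninfected men and women", so 24 is the upper limit for paired samples in any condition. Section 10.1 fixes the doses: "The dosing condition will be examined as an ordinal variable: 2, 4, and 7 doses/week".

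A second exploratory endpoint is also stated as a correlation: "The correlation between intracellular tenofovir-diphosphate concentrations and tenofovir hair concentrations on the last day of each dosing period will be determined".

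The ratios described in sections 10.1 and 10.3 compare dosing conditions with each other, not one hair type with the other.

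**The concern.** The question in section 8.6 is about substitution, and the statistic named to inform it measures something else. Correlation describes how closely two measurements follow a straight line. It says nothing about whether they give the same value. Level matters here because section 3.1 foresees using the biomarker to find an exposure threshold, and section 10.3 judges discrimination by whether levels under one dosing condition exceed those under another. If pubic hair ran consistently higher or lower than scalp hair, a threshold derived from scalp hair would misclassify pubic samples, and the correlation would give no warning.

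The second issue is what drives the correlation. Both hair types are sampled under three doses set by the design. Both should rise with dose, so a coefficient calculated over all conditions is positive for that reason alone, before any further person-level link between the two matrices is shown. The same applies to hair versus intracellular TFV-DP if that correlation is pooled.

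**Working it through.** The protocol gives no target correlation, acceptance limit or sample-size basis for this comparison, so there is no stated figure to reproduce.

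**Inputs**
- Doses of 2, 4 and 7 per week (section 10.1).
- At most 24 participants (section 5). The number giving pubic hair is unknown because it is optional (section 8.6), so 24 and 12 are used.
- Log-scale SD at fixed dose, s: not given. Section 10.4 says there are no preliminary data on variability in hair-level ratios or on within-person correlation. Assumed range: 0.3, 0.5, 0.7.
- Assumption: both hair types are proportional to dose.

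**Step 1: difference in level.** If pubic = k × scalp for every person, r = 1.0 on the raw and the log scale, for any k > 0. The steps between adjacent conditions are 7/4 = 1.75 and 4/2 = 2.
- k = 1.75: pubic hair at 4 doses/week reads like scalp hair at 4 × 1.75 = 7.
- k = 2: pubic hair at 2 doses/week reads like scalp hair at 2 × 2 = 4.
- k = 0.5: pubic hair at 7 doses/week reads like scalp hair at 7 × 0.5 = 3.5, and at 4 like 2.

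In a simulated data set (24 people, three doses, s = 0.5) with k = 0.5, r was 1.00 and Lin's concordance coefficient was about 0.60. With k = 0.25, r was again 1.00 and concordance about 0.25.

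**Step 2: correlation supplied by the doses.** The logs of 2, 4 and 7 are 0.693, 1.386 and 1.946, with mean 1.342. Their variance is V = (0.4208 + 0.0020 + 0.3650)/3 = 0.2626. If the correlation within a condition is ρ, the pooled log-scale correlation is

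r = (V + ρs²)/(V + s²).

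With ρ = 0 this becomes V/(V + s²):

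| s | Pooled r when ρ = 0 |
|---|---|
| 0.3 | 0.2626/(0.2626 + 0.09) = 0.745 |
| 0.5 | 0.2626/(0.2626 + 0.25) = 0.512 |
| 0.7 | 0.2626/(0.2626 + 0.49) = 0.349 |

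**Step 3: simulation** (2,000 runs, ρ = 0, k = 0.5). Means, for s = 0.3 / 0.5 / 0.7:

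| Quantity | n = 24 | n = 12 |
|---|---|---|
| Pooled log-scale r | 0.75 / 0.52 / 0.35 | 0.75 / 0.52 / 0.36 |
| Mean within-condition r | 0.00 / 0.00 / 0.00 | 0.00 / 0.00 / 0.00 |
| Geometric mean pubic:scalp ratio | 0.50 / 0.50 / 0.51 | 0.50 / 0.50 / 0.51 |
| Raw-scale concordance | 0.34 / 0.24 / 0.16 | 0.34 / 0.25 / 0.17 |

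With n = 24 the pooled r was nominally significant in about 100%, 100% and 89% of runs. Raw-scale pooled r was 0.67 / 0.41 / 0.25. It rose to 0.81 / 0.59 / 0.41 when enrollment samples, taken as zero, were included. The ratio and the within-condition correlation show what the pooled correlation hides.

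**The case against.** Several points on the other side have force.

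- **No decision rule.** A reader might infer that a high correlation would be taken as proof of interchangeability. The documents do not support that. Section 8.6 says only that the correlation will assist the judgement, speaks of substitution as a possibility, and sets no cut-off. The aim is exploratory and the specimen optional. This stands, and it limits the importance of the point.
- **Other summaries would reveal an offset.** Section 10.3 promises summary statistics and graphs for all aims, and a clear difference in level would probably be seen there. This stands in part: general summaries are not a paired agreement analysis.
- **An alternative specimen may have its own scale.** No passage plans to read pubic levels against scalp values. Samples taken under all three conditions would permit a conversion factor. That is true, but no calibration is planned, and correlation does not supply one.
- **Pooling is not stated.** The endpoint wording can mean a separate correlation within each condition. On that reading the dose-driven part disappears and only the level part remains.
- **Zero association within a condition is extreme.** Section 3.1 holds that hair levels follow blood levels, and a person's two hair types share the same blood, so ρ is probably above zero. The calculation shows what the doses contribute by themselves; it does not forecast the result.
- **Tracking dose is part of the purpose.** A pubic level that rises with dose is relevant evidence, though not sufficient for substitution.

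**Conclusion.** The point holds as a minor one. Correlation is the only measure named for scalp versus pubic hair, and it cannot detect a constant difference in level, even one as large as the step between adjacent dosing conditions (1.75 or 2, assuming proportionality). This part does not depend on how the correlation is calculated.

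The dose-driven part is conditional. It applies only if conditions are pooled. Its size, about 0.75 to 0.35, rests on an assumed log-SD of 0.3 to 0.7 and on no association within a condition. It would be wrong to say that the correlation will be produced by the doses alone.

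A reader might also take s from the plasma AUC spread in section 3.2.5 (685/2287 = 0.30) and treat r = 0.75 as supported by the protocol's own data. That does not follow: plasma exposure is common to a person's two hair types, so it cannot serve as independent noise. The range of s remains an assumption.

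For hair versus TFV-DP only dose adjustment is at issue. These are different analytes, so agreement in level is not the question, and no passage says that the result will be read as validity in the individual. No primary objective is affected.

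**What to change.** In section 8.6 and the exploratory endpoint:

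1. Keep correlation as a descriptive measure. Report it within each dosing condition or adjusted for condition, for pubic versus scalp hair and for hair versus TFV-DP, with allowance for repeated measures on each participant. Label any pooled value as partly due to assigned dose.
2. Add the paired pubic:scalp ratio: geometric mean and 95% limits of agreement on the log scale, by condition and overall.
3. Check whether the ratio is constant across 2, 4 and 7 doses/week. If it is constant but not 1, present it as a conversion factor rather than as evidence of interchangeability.

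The cost is a change of wording and a little more analysis; no new samples or visits are needed. The correlations will look less favourable than pooled ones. The limits of agreement may be wide, because pubic hair is opt-in and at most 24 participants can contribute.
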